### Intervention description {11a}

Group-based psychoeducation for relatives. Group size: 20–40 relatives. Duration of intervention: six sessions over 6–10 weeks, each session is 2 h long including a 15-min break. The sessions are held by experienced clinicians from the Copenhagen Affective Disorder Clinic, one chief physician, and one nurse. Each session focuses on a specific topic, which the clinicians present and discuss using a presentation viewer. The sessions are interactive, and the participants are encouraged to ask questions during the presentations. During each session, the participants will have some discussions in smaller groups to reflect on topics raised during the session.

The topics of the sessions are:Introduction (Information about the clinic, introduction of the clinicians and participants, expectations alignments)Bipolar disorder (the diagnosis and challenges in diagnosis)Medical treatment (which medication is used and why)Psychological treatment (psychoeducation for patients)Living with a bipolar disorder (a guest lecturer with lived experience with BD tells his own story of living with BD)Being a relative.

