### Trial design {8}

The trial is designed as a two-arm, parallel-group, superiority, randomized trial with a balanced randomization 1:1 to group-based psychoeducation versus a waiting list [38]. The control waiting list group will be offered participation in group-based psychoeducation (active intervention) during the following half year. The trial is planned and will be conducted in concordance with the CONSORT 2010 Explanation and Elaboration: updated guidelines for reporting parallel group randomized trials [39].

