### Recruitment {15}

Patients at Copenhagen Affective Disorder Clinical are routinely informed about the possibility of psychoeducation for their relatives. If interested, the patients will hand in a registration form with the name and phone numbers of their relative(s). The clinic generally recommends that patients start in psychoeducational group therapy themselves before their relatives are enrolled in psychoeducation. This is however only a recommendation and not a rule. Relatives’ psychoeducation groups are offered once in the autumn and two during spring.

Data from patients with BD are collected from the A-bipolar study, which is a parallel ongoing study [42]. We will secure written consent from the participants in the A-bipolar study to utilize their data in the R-bipolar study.

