## Statistical methods

### Statistical methods for primary and secondary outcomes {20a}

#### Statistical analyses

Analyses will be conducted for the total sample of 200 relatives and their corresponding patients with BD. Two-level linear mixed-effect models will be used including a fixed effect of group (active group versus control) and a person-specific random effect allowing for individual variation in mood instability or other outcome measures.

In relation to hypothesis 3, it will be investigated whether mood instability in patients and relatives covary more than mood instability in patients and healthy control individuals (controls collected as part of the ongoing Bipolar Illness Onset (BIO) study in the Copenhagen Affective Disorder Clinic [77].

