## Discussion

This protocol describes our currently ongoing randomized controlled trial (RCT) that aims at investigating group-based psychoeducation as an intervention for relatives of individuals diagnosed with bipolar disorder (BD). The study is the first large-scale real-world RCT to focus on a relatively short intervention of psychoeducation (6 sessions of 2 h each) in a large group of relatives (approximately 30 participants per group). With this focus, we wish to test an intervention that is feasible to implement in real-life psychiatric settings with limited budgets and time. It is also the first study to use mood instability in relatives as the primary outcome measure and to investigate whether mood instability and other affective symptoms in patients and relatives covary. It could be considered as limitations, that the trial is not blinded and does not include long-term follow-up.

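### The active arm is treated in shared courses but the stated model and sample size have no course term, so type I error exceeds 5% if outcomes correlate within course

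*Protocol article*

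**What the plan says.** Intervention description {11a} sets the course size ("Group size: 20–40 relatives"), and the Discussion gives about 30 as typical. The six sessions are interactive, and at each one "the participants will have some discussions in smaller groups to reflect on topics raised during the session". Recruitment {15} states that "groups are offered once in the autumn and two during spring", so three courses a year.

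Trial design {8} describes "balanced randomization 1:1 to group-based psychoeducation versus a waiting list". Controls therefore share no course during the randomised comparison; they are offered one afterwards.

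The Statistical analyses section names a two-level linear mixed model with "a fixed effect of group (active group versus control) and a person-specific random effect". Sample size {14} starts from 126 and adjusts for two relatives of one patient (30%) and for dropout (10%), giving 180. Sequence generation {16a} allocates relatives of the same patient together because they are not independent. No section mentions a course effect, an ICC or a design effect.

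**The concern.** This is a partially nested design. Relatives in the active arm share a course, with its discussions, composition and timing; controls share nothing comparable. If those shared conditions move outcomes together, the active-arm mean varies more than independent observations would. The two levels of the stated model are observation and person, so course has no place in it. The article accepts that dependence matters when two relatives belong to one patient, but does not consider the larger shared unit.

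At stake are the interval and p-value for the primary outcome and for every secondary outcome measured in relatives. The article also aims to support use of this format in routine services. That is a statement about future courses, so variation between courses belongs in the uncertainty.

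**Working it through.** **The plan's own figure.** 126 × 1.3 × 1.1 = 180.2, which reproduces the stated 180. The two stated inflations use up the whole step, so no course factor is included.

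**Active trial participants per course (m), an assumption.** Trial status gives recruitment from April 2022 to January 2024, about 21 months, with 185 relatives included. At three courses a year, 21/12 × 3 ≈ 5.25, so 5 to 6 courses. Half of 185 is 92.5; 92.5/6 = 15.4 and 92.5/5 = 18.5. I use m = 15 and m = 18.

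**ICC, an assumption.** The article gives none. I use 0, 0.01, 0.02 and 0.05.

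**Formulas** (clustering in the active arm only, equal arms):
- Active-arm design effect: DE = 1 + (m − 1) × ICC
- True over assumed variance of the arm difference: R = (DE + 1)/2
- Actual two-sided type I error at nominal 5%: 2 × (1 − Φ(1.96/√R))

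Example, m = 18 and ICC 0.05: DE = 1 + 17 × 0.05 = 1.85; R = 2.85/2 = 1.425; √R = 1.194; 1.96/1.194 = 1.642; type I error = 10.1%.

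| m | ICC | DE | R | √R | Type I error |
|---|---|---|---|---|---|
| 15 or 18 | 0 | 1.00 | 1.000 | 1.000 | 5.0% |
| 15 | 0.01 | 1.14 | 1.070 | 1.034 | 5.8% |
| 18 | 0.01 | 1.17 | 1.085 | 1.042 | 6.0% |
| 15 | 0.02 | 1.28 | 1.140 | 1.068 | 6.6% |
| 18 | 0.02 | 1.34 | 1.170 | 1.082 | 7.0% |
| 15 | 0.05 | 1.70 | 1.350 | 1.162 | 9.2% |
| 18 | 0.05 | 1.85 | 1.425 | 1.194 | 10.1% |

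The column √R is the factor by which the standard error is understated: 3–4%, 7–8% and 16–19%.

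**Check by simulation.** With 100 active relatives in 5 courses of 20 (40,000 simulated trials per cell), the course-blind test rejected in 6.2%, 7.3% and 10.6% of null trials at ICC 0.01, 0.02 and 0.05. The formula at m = 20 gives 6.1%, 7.2% and 10.7%. In the simulations with ICC 0 the rate was about 5%.

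**How well k courses can estimate the course variance.** The analysis-of-variance estimate is zero or negative when the between-course mean square does not exceed the within-course one. The probability is P(F ≤ 1/(1 + m × ICC/(1 − ICC))), with k − 1 and k(m − 1) degrees of freedom. For 5 courses of 18 or 6 courses of 15, this is about 49–50%, 42–43% and 27% at true ICC 0.01, 0.02 and 0.05.

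**The case against.** The strongest reply is that nothing shows the ICC to be positive. The primary outcome is each relative's own daily app rating, not something scored in the session or by the course leaders. Intervention description {11a} names one physician, one nurse and one guest lecturer. If the same people run every course, which the article does not state, their influence is common to the whole arm and adds no variation between courses. Season is partly shared with controls recruited over the same period. All of this stands: it makes a small ICC plausible and is why the result must be conditional. It does not remove course-specific discussion and composition.

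Three stronger readings are tempting.
- A reader might infer that the type I error is inflated as a matter of fact. The article does not support that without an ICC.
- A reader might take m to be the full course size of 20 to 40. What counts is active-arm trial participants per course. Former controls also take seats, other relatives may attend, and 25 of the 185 had already dropped out. At m = 10 the error would be 5.5%, 6.0% and 7.7% at the same three ICCs.
- A reader might convert the design effect into a loss from 80% power. The 126 does not follow from a difference of 0.2 with SD 2.6, so 80% is not a sound starting point. That is a separate issue.

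One may also say that an article condenses its full protocol. That helps only in part, because the model is stated, and stated as two-level.

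**Conclusion.** The point holds in conditional form. The article fixes a model and a sample size with no course term for an arm treated in shared courses. For any positive within-course correlation, the course-blind standard error is too small and the test rejects too often. With 15 to 18 active trial participants per course, the excess over 5% is about one percentage point at ICC 0.01, about two at 0.02, and four to five at 0.05; at ICC 0 there is none. These figures rest on the assumed number of courses, an even split between arms and over courses, and assumed ICCs. The article does not show which ICC applies. The plan should be changed because the analysis as written cannot show whether its conclusion depends on this.

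**What to change.** In the Statistical analyses section, add a random intercept for course in the active arm only. Include a patient-level (family) random effect in both arms, since the article itself treats co-relatives as dependent and the stated model has no term for them. Use small-sample degrees of freedom such as Satterthwaite or Kenward–Roger. Define course as the one scheduled at allocation, not the one attended, so that the randomised comparison is preserved. Report the estimated course ICC.

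The random intercept alone is not enough. With 5 to 6 courses its variance will often be estimated as zero, and the model then falls back to the one criticised here. Even a course-aware test with only 3 courses had a type I error of about 6–7% in simulation. So also report the treatment effect and its interval over a fixed range of assumed ICCs, for example 0 to 0.05, and state that a zero estimate is not evidence of independence.

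The cost is wider intervals and few course-level degrees of freedom. With about 4, the critical value approaches 2.8 if course variance dominates. The scheduled course must be on record for each relative. Data management {19} does not list it among the logbook items, so this needs checking. The change adds no outcome assessments and does not alter recruitment.

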### Criteria for discontinuing or modifying allocated interventions {11b}

There are no criteria for discontinuing or modifying the allocated intervention for the individual participant.

### Strategies to improve adherence to interventions {11c}

The participating relatives are reminded about the research project because of their use of a smartphone-based monitoring system (The Monsenso app), which is presented below. After the psychoeducation, the participating relatives are asked to specify how many of the six sessions they attended, as a part of the final questionnaire.

### Relevant concomitant care permitted or prohibited during the trial {11d}

We cannot, nor should we, control if the participants seek guidance and information in other arenas.

### Provisions for post-trial care {30}

N/A. Owing to the nature of the intervention, we have no provisions.

### Outcomes {12}

The outcomes listed below are for (1) relatives to patients with BD and (2) the corresponding patients with BD.

Figure 1 shows an overview of the schedule of the study.

**Fig. 1 Fig1:**
[figure not shown]
Spirit study schedule of enrolment, interventions, and assessments

*Primary outcome*: Daily self-reported mood instability collected via the Monsenso app^1^ [43] for relatives during the period in which the participants are part of the research project.*Secondary outcomes*: Other critically daily self-reported smartphone-based data including daily activity level, anxiety, irritability, stress, cognition, sleep, alcohol consumption, caregiver burden, and medicine as reported in [44].

Clinically rated observer-based scores on the following three scales: Hamilton Depression Scale-6 items (HAM-D6) [45] (being more sensitive in RCTs than the HAM-D17 [46]), the Young Mania Rating Scale (YMRS) [47] and the Functional Assessment Short Test (FAST) (a 24-item interviewer-administered interview concerning autonomy, occupational functioning, cognitive functioning, financial issues, interpersonal relationships and leisure time) [48].

Self-assessed scores on the following questionnaires: Burden Assessment Scale [49], Perceived Criticism Measure [22, 50], Carer Quality of Life [51, 52], Carer-Self-Efficacy [34, 53], Bipolar Knowledge Scale [54], Short Form-12 [55, 56], Brief Symptom Inventory [57], Perceived Stress Scale [58], Mood Disorder Questionnaire [59], Major Depression Inventory [60, 61], Childhood Trauma Questionnaire (CTQ) [62]. When the questionnaires are repeated after the intervention, the.

participants are asked to complete a satisfaction survey on the psychoeducation. The satisfaction survey was developed in close collaboration with the clinicians from the Copenhagen Affective Disorder Clinic.

*Tertiary outcomes*: Automatically smartphone-generated data on physical [63], and social activity [64].

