**Methods:**

The trial is designed as a two-arm, parallel-group randomized trial with a balanced randomization 1:1 to either group-based psychoeducation or a waiting list for approximately 4 months and subsequent group-based psychoeducation. The primary outcome measure is mood instability calculated based on daily smartphone-based mood self-assessments. Other relevant outcomes are measured, including patients’ reported outcomes, assessing self-assessed burden, self-efficacy, and knowledge about BD.

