## Interventions

### Explanation for the choice of comparators {6b}

We have chosen to compare the group-based psychoeducation intervention with a control group on a waiting list. We aim to investigate and evaluate clinical practice in an ongoing real-world intervention in comparison with its actual alternative: no group-based psychoeducation. The two-armed parallel group randomization also makes it possible to optimize the data yield because participants who are randomized to the control group will also participate in the intervention group afterwards.

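### The primary outcome window does not end when waiting-list relatives receive the course, so the randomised comparison is open to control days recorded after crossover

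*Protocol article*

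**What the plan says.** All references are to the protocol article.

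- **Outcomes {12}:** the primary outcome is mood instability from the app, taken "for relatives during the period in which the participants are part of the research project". No start or end day is given in the text.
- **Abstract, Methods:** controls have "a waiting list for approximately 4 months and subsequent group-based psychoeducation". Trial design {8} adds that they "will be offered participation in group-based psychoeducation (active intervention) during the following half year".
- **Explanation for the choice of comparators {6b}:** the design is said to make it possible to "optimize the data yield because participants who are randomized to the control group will also participate in the intervention group afterwards".
- **Statistical analyses {20a}:** a two-level mixed model "including a fixed effect of group (active group versus control) and a person-specific random effect". No term for period, time or exposure is named.
- **Estimation of mood instability:** squared successive differences are combined into one rMSSD per participant over follow-up. No division into waiting and treated periods is mentioned.
- **Trial status:** recruitment began in April 2022 and was due to close at the end of January 2024, with data gathering complete in May 2024.

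**The concern.** Every control is offered the same course that is being tested. A window defined as time in the project therefore covers treated as well as untreated days for any control who goes on recording after crossover. Later participation can add data only if something is recorded then, and section {6b} presents this as an advantage of the design.

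If such days reached the primary model, it could not separate them. There are two ways they could enter:

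- **Left under control.** The control mean then includes treated days, and a true benefit is pulled toward zero.
- **Relabelled as active.** The contrast then becomes partly before-after within the same people, and treatment is mixed with time on the app and season.

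Neither is the 1:1 comparison of active course with waiting list that Trial design {8} sets out. What is at stake is the meaning of the primary estimate as well as its precision.

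**Working it through.** **1. The plan's own sample size.** Sample size {14} gives a difference of 0.2, SD 2.6, 80% power and type 1 error 0.05 (two-sided assumed), with 126 in total. With n per arm = 2 × (1.960 + 0.842)² × SD² / difference², those inputs give 2,653 per arm, or 5,306 in total. The stated 126 does not reproduce. That is a separate matter, but it fixes the baseline used here: 126 (63 per arm) is what a standardised effect of 0.5 requires, since 2 × (2.802)² / 0.5² = 62.8. I use 0.5 SD only because it is the effect implied by the stated number.

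**2. Assumptions the article does not supply.** The wait is 4 × 52/12 = 17.3 weeks. The effect is full and immediate at crossover. Days average linearly. The SD is unchanged. Post-crossover recording lasts 6 or 10 weeks (the course lengths in Intervention description {11a}) or 26 weeks (a half year, as an outer case).

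**3. Dilution if those days stay under control.** The post-crossover share is f = w / (17.3 + w), the retained effect is 0.5 × (1 − f), and power is Φ(effect × √(63/2) − 1.96).

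| Weeks after crossover (w) | f | Effect (SD) | Effect kept | Power, 63 per arm | Total N for 80% power |
|---|---|---|---|---|---|
| 0 | 0 | 0.50 | 100% | 80% | 126 |
| 6 | 0.257 | 0.371 | 74% | 55% | 228 |
| 10 | 0.366 | 0.317 | 63% | 43% | 314 |
| 26 | 0.600 | 0.200 | 40% | 20% | 786 |

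Example for 10 weeks: 10/27.3 = 0.366; 0.5 × 0.634 = 0.317; 0.317 × 5.612 − 1.96 = −0.18; Φ(−0.18) = 0.43.

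**4. Sensitivity to the rMSSD form.** rMSSD averages squares, so the linear step is an approximation. With an untreated level of 4.1 and a difference of 1.3 (0.5 × 2.6), the control value is √[(1 − f) × 4.1² + f × 2.8²]. The share kept is that value minus 2.8, divided by 1.3. This gives 78%, 68% and 45% for 6, 10 and 26 weeks, slightly less dilution with the same pattern.

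**5. The relabelling case.** Its bias depends on how mood instability changes with time on the app and with season. The article gives no figure for either, so I give no size.

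**6. The dates.** End of January to May 2024 is about 4 months, the same as the stated wait. For the last controls enrolled, recording would therefore end at about the time the wait ends. For controls enrolled from April 2022 onward, these dates set no such limit.

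**The case against.** The strongest reply is that no passage puts post-crossover control days into the randomised comparison. The trial is described as a parallel-group comparison with a waiting list, and the model compares active with control. Time in the project may simply mean the comparison phase of about 4 months, which is an unbiased reading and fits the Trial status dates. The remark on data yield sits in a section on the choice of comparator and could refer to a separate pre-post or satisfaction analysis. The schedule in Fig. 1 is not shown and may define the window, and an article may leave day filters to the full protocol.

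Much of this stands. A reader might infer that the contrast is in fact contaminated, or that contamination differs by recruitment date. The article supports neither, because it does not state how long earlier controls go on recording or how those days are used. A reader might also see a contradiction between a wait of about 4 months and a course offered within the following half year. These are compatible, given that "psychoeducation groups are offered once in the autumn and two during spring". Nor is it an error for the active arm's window to include days before or during the course, since counting from randomisation is ordinary practice in a pragmatic trial.

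What does not stand is that this is only omitted detail. The article does state a window, and as worded it runs past crossover. It also states a reason for valuing data from that period and a model that could not tell the two periods apart.

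**Conclusion.** The point holds as an unbounded window, not as demonstrated bias. Outcomes {12}, section {6b} and Trial status do not fit together as written. If participation ends at about 4 months for everyone, the outcome text should say so, and the claimed gain in data needs another explanation. If it runs longer, the primary comparison needs an explicit cut-off.

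The tabulated losses are conditional on post-crossover days being kept under control, and on the assumed recording length, onset of effect and 0.5 SD baseline. A slower onset or shorter recording would reduce them. With no post-crossover days in the comparison, there is no loss from this source.

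**What to change.** Before group codes are revealed:

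1. Define the primary rMSSD over one window that is the same for both arms of a course round and ends before that round's controls attend their first session (about 4 months).
2. State that all participants are analysed in the arm to which they were randomised, and that controls are not relabelled as active in the primary model.
3. Label post-crossover control data as a separate, non-randomised before-after analysis, and reword section {6b} so that the extra data clearly refer to that analysis.
4. Bring Outcomes {12}, section {6b} and Trial status into line on how long relatives record.

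The cost is a change of wording and a date filter on app data that are collected anyway. The downside is that fewer app days, and so fewer pairs of consecutive days, enter each participant's primary rMSSD.
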